#### RCT

First, the baseline characteristics of the two groups will be examined using independent samples *t* tests or Mann-Whitney *U* tests (depending on the distribution values). A χ^2^ test will be used to examine dichotomous variables. Next, the effectiveness of the intervention on the primary outcome measure (CASP-DLV parent-reports) will be assessed using multilevel analysis (i.e., random coefficient analysis) for both short-term (3 months after injury) and long-term (6 months after injury) outcomes. Time of measurement, group assignment (control or intervention group) and the interaction between time of measurement and group will be included in the multi-level regression model. The level of significance will be *p* < 0.05. The random coefficient analysis will be performed with all of the participants using intention-to-treat analyses. For those with incomplete datasets, longitudinal imputation techniques will be used [66].

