### Sample size

Sample size calculations for the cohort study are based on the available literature about MTBI prevalence and the expected number of participants who may visit the participating hospitals. Based on an inclusion period of 2 years, the aim is to recruit a sample of 500 children and adolescents who have experienced an MTBI. Assuming a 10 % dropout rate [64], our final sample should include 450 participants. Previous research shows that approximately 20 % of the population will experience long-term problems [13–16, 20–24, 30, 36] after an MTBI. Therefore, approximately 90 of our participants will experience long-term problems. When conducting the regression analysis to identify the predictors of the presence of long-term problems, we should include nine determinants, based on the assumption that approximately ten participants per determinant are needed for a reliable analysis [65].

Sample size calculations for the RCT are based on the results of studies on paediatric traumatic brain injury patients’ participation that relied on the parent-reports of the CASP-DLV. For the CASP-DLV, a standardized difference of 0.5 was expected [48]. With an α of 0.05 and a power of 0.8, a minimum of 63 children per group (control group and intervention group) is required for sufficient statistical power. Assuming a dropout rate of 10 %, the aim is to recruit at least 140 children and adolescents for the RCT.

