#### Cohort study

To determine the results of the primary outcome measure (CASP-DLV parent-reports), descriptive statistics will be used. Continuous variables will be expressed as the means and standard deviations or as medians with interquartile ranges, depending on the distribution values. Repeated-measures analysis of variance will be used to determine the difference in activities and participation over time. If a significant difference between the measurement points (*p* < 0.05) is found, a post hoc analysis based on Levene’s test will be performed.

Linear regression analysis will be used to identify the outcome predictors of activities and participation at 6 months post-injury, as measured by the CASP-DLV parent reports. Within 2 weeks after the injury, both continuous and categorical variables (i.e., injury and non-injury-related factors) are measured, as well as pre-injury family functioning (FAD-GF) and behaviour (CBCL); degree of fatigue (PedsQL-Fatigue); quality of life (PedsQL-QoL); sensory processing (SP/AASP-NL); physical, cognitive, emotional and behavioural post-concussive symptoms (HBI); post-traumatic stress (Schokverwerkingslijst [Impact of Event Scale–Dutch language version]); and participation in after-school activities (CAPE). Each variable will first be examined using univariate linear regression analysis to predict activities and participation. Next, variables with values of *p* < 0.2 in the univariate linear regression analysis will be included in the multivariate linear regression analysis. In the multivariate linear analysis, the significance level will be set at *p* < 0.05. For more clinically relevant purposes, outcome predictors will also be determined using logistic regression analyses. If the intervention is found to be effective (see statistical analyses of RCT study below), the data of the intervention group will be excluded from all of the cohort study analyses.

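### The RCT assesses effectiveness at both 3 and 6 months at an unadjusted p < 0.05, and no primary time point or rule for calling the intervention effective is fixed

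*Protocol article*

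**What the plan says.** The section on the RCT analysis evaluates the intervention on the parent-reported CASP-DLV by a multilevel model, "for both short-term (3 months after injury) and long-term (6 months after injury) outcomes". The model contains time, group and their interaction. One significance level, p < 0.05, is given for the analysis. The section does not say which coefficient or contrast answers the question of effectiveness.

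The other places that bear on the choice are these:

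- **Background.** The hypothesis concerns the whole of the first 6 months and singles out no visit.
- **Table 3.** The CASP-DLV parent report is marked as primary and is measured at T0, T1 and T2 alike.
- **Sample size.** "For the CASP-DLV, a standardized difference of 0.5 was expected", with no time point attached. "With an α of 0.05 and a power of 0.8", "a minimum of 63 children per group (control group and intervention group) is required". After allowance for 10% dropout, "the aim is to recruit at least 140 children and adolescents for the RCT".
- **Cohort study analyses.** "If the intervention is found to be effective (see statistical analyses of RCT study below"), the intervention arm's data are removed from every cohort analysis. The Outcome measurements section says the same. The cross-reference leads to the RCT section, which contains no such rule.

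**The concern.** The outcome instrument is fixed, but the time at which it decides the trial is not. Two assessments of effectiveness share one unadjusted 5% level, while the sample size allows for a single comparison. If the result is significant at one visit and not at the other, the protocol gives no agreed reading, and the choice would be made after the group results are known.

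Two things depend on that choice. The first is the trial's own conclusion: the Discussion foresees direct use in daily practice once effectiveness is shown. The second is the composition of the cohort. With 1:1 allocation, half of 140, or 70 of the planned 500 children, stay in or drop out of all cohort analyses on a criterion that is nowhere written down.

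**Working it through.** **1. The plan's own figure.** Inputs from the Sample size section: standardized difference 0.5, α 0.05, power 0.8, dropout 10%. Sidedness is not stated.

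- n per group = 2 × (1.960 + 0.842)² / 0.5² = 62.8, rounded up to 63. A one-sided α would give 50, so the calculation is two-sided.
- Recruitment: 126 / 0.90 = 140.
- Power with 63 per group: 0.801.

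The figures reproduce exactly, for one two-sided comparison at 0.05.

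**2. Error if either time point suffices.** Let Z1 and Z2 be the test statistics for the group difference at 3 and 6 months, bivariate normal under the null with correlation r.

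- Any false significance: 1 − P(|Z1| < 1.96 and |Z2| < 1.96). At r = 0 this is 1 − 0.95² = 0.0975.
- False claim of benefit: 1 − P(Z1 < 1.96 and Z2 < 1.96). For a single test it is 0.025.
- Both significant: 0.05 + 0.05 minus the first quantity.

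The protocol does not give r, so it is an assumption and a range is shown. The only related figure is the test-retest intraclass correlation of 0.90 for the CASP-DLV (Primary outcome measure section), taken here as a rough upper limit.

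| r (assumed) | Either significant, two-sided | False claim of benefit | Both significant |
|---|---|---|---|
| 0 | 9.75% | 4.94% | 0.25% |
| 0.3 | 9.51% | 4.76% | 0.49% |
| 0.5 | 9.07% | 4.54% | 0.93% |
| 0.7 | 8.35% | 4.17% | 1.65% |
| 0.8 | 7.81% | 3.90% | 2.19% |
| 0.9 | 7.04% | 3.52% | 2.96% |

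**3. Error under other rules that the text would also allow.**

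- One joint test of the group differences at both visits has an error of 5%.
- Requiring significance at both visits gives the last column when there is no effect at either visit, and at most 5% when there is an effect at one visit only.

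**4. What the remedies cost.**

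- One primary time point, with the other tested only afterwards in fixed sequence: overall error 5%, and 63 per group and 140 recruited stand.
- Equal split, 0.025 each: 77 per group and 172 recruited (154 / 0.90 = 171.1, rounded up to an even number). With 63 per group it leaves 71% power per time point.

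**The case against.** A reader might infer that the trial carries an 8-9% chance of a false claim of effectiveness. The documents do not support that as a flat statement, for three reasons, and all three stand:

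- The text describes one model and one significance level. It does not say that either time point is enough. The single hypothesis about the first 6 months fits an overall test as well as two separate ones.
- A figure of 8-9% needs a correlation of about 0.5 to 0.8, and the protocol gives none.
- That figure counts false findings in both directions. The hypothesis is that participation increases, so a false claim of effectiveness is a false claim of benefit, and its probability is about half as large.

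It can also be said that contrasts, testing order and multiplicity are usual content of a statistical analysis plan, which is not shown, and that this is a condensed article. That carries some weight for the technical detail. It does not dispose of the point. The time at which the primary outcome is decided belongs to its definition. The article is not silent on it: it places both time points under effectiveness at 0.05. It also makes the cohort analyses depend on a verdict and sends the reader to a section that does not define it.

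Finally, choosing 6 months is partly a matter of judgement. The 6-month endpoint of the cohort regression is weak support, because it serves a different aim. The Discussion justifies the nested design partly by interest in the short-term effect.

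**Conclusion.** The point holds as a badly fixed primary comparison: two time points, one unadjusted level, no primary time point, deciding contrast or order, and an undefined verdict on which the cohort analyses depend. The sample size arithmetic is correct for one comparison; what is missing is a statement of which comparison it powers.

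The inflation is conditional. If significance at either visit counts, two-sided type I error is 7.0% to 9.75% for correlations from 0.9 to 0, and a false claim of benefit is 3.5% to 4.9% against 2.5%. These figures assume normal test statistics and no effect at either visit. No correlation in that range brings the error back to 5%. Under a joint test, or a rule requiring both visits, there would be no inflation. That the document does not say which rule applies is the defect; the inflation is its possible consequence, not an established property of the trial.

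**What to change.** State one decision rule before group results are examined. The preferred form is:

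- The primary comparison is the group difference in the CASP-DLV parent report at 6 months (T2), estimated from the multilevel model and tested at two-sided 0.05.
- The 3-month difference (T1) is tested at two-sided 0.05 only if the 6-month difference is significant.
- Effectiveness, including for the exclusion of intervention-arm data from the cohort analyses, means a significant 6-month difference in favour of the intervention.
- The calculation of 63 per group refers to the 6-month contrast.

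The 6-month choice follows the aim, stated under Intervention procedures, of preventing long-term problems. A joint test, or success required at both visits, would also control the error and would be acceptable if stated. The latter costs power: with 80% at each visit, the chance of success at both lies between 0.8 × 0.8 = 64% (independent) and 80%.

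The cost of the preferred form is a few sentences. The 6-month test loses no power and the target of 140 is unchanged. The downside is that an effect seen only at 3 months becomes supportive and not confirmatory. The sponsor should accept this openly, since the Discussion also gives short-term insight as a reason for the design.

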### Randomisation procedures

Participants who agree to be included in the RCT are randomly assigned to either the intervention group or the control group. Randomisation is performed after the T0 measurement, which takes place within 2–4 weeks post-injury. It is performed by an independent person who is not involved in the recruitment, intervention or outcome measurements. The randomisation is performed using an online randomisation program that employs computerized block randomisation, and the randomisation scheme includes stratification based on three variables: age (6–12 years or 12–18 years), gender (male or female) and location (hospital). Caregivers are assigned to the same group as their child. After randomisation, the independent third person informs the interventionist (a professional experienced and educated in child rehabilitation after TBI) about the patients assigned to the intervention group, whereupon appointments for the intervention are scheduled.

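### The stated RCT model does not adjust for the T0 CASP-DLV score or the stratification factors, which forgoes precision but does not undo the planned 80% power

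*Protocol article*

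**What the plan says.** The RCT part of the Statistical analyses section of the protocol article assesses the parent-reported CASP-DLV by random coefficient analysis for 3-month and 6-month outcomes. It names the model terms: "Time of measurement, group assignment (control or intervention group) and the interaction between time of measurement and group will be included". No covariate is mentioned. The same paragraph begins with tests between the arms: "First, the baseline characteristics of the two groups will be examined using independent samples".

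Under Randomisation procedures, randomisation follows the T0 measurement, and "the randomisation scheme includes stratification based on three variables": age group, gender and hospital. Table 3 shows the parent CASP-DLV collected at T0, T1 and T2. The RCT paragraph does not say whether T0 is one of the modelled time points.

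Under Sample size, "a standardized difference of 0.5 was expected", and then "With an α of 0.05 and a power of 0.8, a minimum of 63 children per group". With 10% dropout the target is at least 140. The calculation uses no covariate and no correlation between T0 and follow-up.

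**The concern.** The T0 score of the primary outcome is usually the strongest single predictor of the later score, and it is measured before allocation. Age group, gender and hospital are also fixed before allocation and are built into the randomisation. A model that uses none of them as covariates gives up precision that costs nothing to obtain.

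Leaving out stratification factors has a second effect. Stratification removes part of the chance difference between arms, but a model without the factors still counts that part in its standard error. If the factors are prognostic, the reported standard error is too large and the test rejects too seldom.

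The role of T0 is also open. If T0 is a modelled time point with free arm means, the time-by-group term measures change from T0. If only T1 and T2 are modelled, the T0 information is unused. The time-by-group term then says only whether the effect differs between 3 and 6 months. The effect itself is the group contrast at each time.

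The result matters beyond the RCT. If the intervention is found effective, the intervention arm (about 140/2 = 70 of 500 children) is excluded from the cohort analyses.

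**Working it through.** **Inputs from the Sample size section:** α 0.05, power 0.8, standardized difference d = 0.5 (so SD = 1), 63 per group, 10% dropout, 140 recruited. Sidedness is not stated. A one-sided test would need 50 per group, so the plan's figure is two-sided.

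**Assumed, because the article gives no value:** ρ, the correlation between T0 and follow-up CASP-DLV; R², the share of outcome variance explained by the stratification factors; and equal SDs at T0 and follow-up (used for the change contrast). The test-retest coefficient of 0.90 quoted for the CASP-DLV describes reliability. It is not the correlation across months of recovery, so it does not supply ρ.

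**1. The plan's own figure.** n per group = 2(1.960 + 0.842)²/0.5² = 62.8, rounded up to 63; 126/0.9 = 140. Both reproduce. Power at 63 per group is 80.1% by the normal formula and 79.5% by the t-test. This is an unadjusted two-group comparison.

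**2. Adjusting for T0.** The residual SD becomes √(1 − ρ²), so the effective difference is 0.5/√(1 − ρ²). At ρ = 0.5 this is 0.5/0.866 = 0.577.

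**3. Change from T0.** The SD of change is √(2(1 − ρ)), so the effective difference is 0.5/√(2(1 − ρ)). At ρ = 0.3 this is 0.5/1.183 = 0.423.

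Power at 63 per group (t-test, two-sided 0.05):

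| ρ (assumed) | Unadjusted follow-up score | T0 as covariate | Change from T0 |
|---|---|---|---|
| 0.2 | 79.5% | 81.1% | 59.5% |
| 0.3 | 79.5% | 83.1% | 65.3% |
| 0.5 | 79.5% | 89.5% | 79.5% |
| 0.7 | 79.5% | 97.4% | 94.9% |

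By the normal formula, T0 adjustment would need 58, 48 and 33 per group for 80% power at ρ = 0.3, 0.5 and 0.7. The change contrast would need 88 at ρ = 0.3.

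**4. Leaving out the stratification factors.** After stratified randomisation the true standard error is about √((1 − R²)·2/63), while the unadjusted model reports √(2/63) = 0.178. Then type I error = 2[1 − Φ(1.96/√(1 − R²))] and power = Φ[(0.5 − 1.96 × 0.178)/(0.178√(1 − R²))]. Adjusted power uses a residual SD of √(1 − R²). All are by the normal formula:

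| R² (assumed) | Unadjusted type I error | Unadjusted power | Adjusted power |
|---|---|---|---|
| 0.05 | 0.044 | 80.7% | 82.1% |
| 0.10 | 0.039 | 81.4% | 84.1% |
| 0.20 | 0.028 | 82.8% | 88.1% |

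A simulation with eight strata, 126 children, an assumed block size of 4 and 4,000 runs per setting agrees. Unadjusted type I error was 0.043 at R² = 0.10 and 0.030 at R² = 0.20. Unadjusted power was 80.2% and 81.5%, and adjusted power 83.0% and 87.7%.

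The gains in steps 2 and 4 are calculated separately and should not be added, since T0 and the stratification factors may explain some of the same variance.

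**The case against.** A reader might infer that omitting these covariates means the stated 80% power is not secured. The documents do not support that. "a minimum of 63 children per group (control group and intervention group) is required for sufficient statistical power" comes from an unadjusted calculation that assumes no gain from covariates, so leaving them out keeps power at about 80%. Omitting the stratification factors does not lower power below plan either (step 4).

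The low figures in the last column of the first table need several conditions together: T0 modelled as an outcome with free arm means, the interaction read as change from T0, the 0.5 standardized on follow-up scores, equal variances, and ρ below 0.5. The article states none of these. If the 0.5 refers to change, power is about 80% at any ρ. If T0 is a modelled time point, it is also not true that baseline is left out; it is present as an outcome but not used as an adjuster. This objection stands in full against any claim of a power shortfall.

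It can also be said that the article is a condensed account, that it does not say no other terms will enter the model, and that a full protocol or SAP may add covariates. This lowers the severity. It does not dispose of the point, because the article goes as far as naming the model terms, and the named set can be improved at no cost.

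The baseline significance tests are a separate and lesser matter. They are uninformative after randomisation, but the article does not use them to choose covariates, and they bear on neither power nor bias.

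**Conclusion.** The point holds as a matter of efficiency and clarity. The stated terms do not adjust for the T0 CASP-DLV or for the factors on which randomisation is stratified. Randomisation still protects the treatment estimate from bias, and the planned sample size is arithmetically correct.

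The size depends on quantities the article does not give. T0 adjustment would raise power from 79.5% to about 83–97% for ρ between 0.3 and 0.7. Omitting factors with R² of 0.10 to 0.20 would take the type I error from 0.05 to about 0.04–0.03; if the factors are not prognostic, this effect vanishes. A shortfall against plan, such as 65% at ρ = 0.3, is conditional on the reading of T0 and of the 0.5 described above and is not established.

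Severity: moderate to minor.

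**What to change.** Model the parent CASP-DLV at T1 and T2 with time, group and time × group, plus T0 CASP-DLV, age group, gender and hospital as fixed covariates. Alternatively, keep T0 as an outcome with the arm means constrained equal at T0, and include the three stratification factors. State that the effects reported are the group contrasts at 3 months and at 6 months. Either form settles the role of T0 and removes the change-from-T0 reading.

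Optionally, describe baseline characteristics by arm without significance tests.

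The cost is analysis wording only. Every variable is already collected, and the covariate form adds about four parameters (one for T0 and one for each two-level factor, as the RCT runs in two hospitals). The sample size need not change. The wording should be settled before outcomes by arm are seen.

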## Discussion

This paper describes the research protocol of the Brains Ahead! study. The study examines the activities and participation outcomes of children and adolescents during the first 6 months after experiencing an MTBI and identifies possible outcome predictors. Furthermore, this study investigates the effectiveness of an early psychoeducational intervention on activities and participation compared with the usual MTBI care received by this population. We chose a nested design because it is preferred to gain insight into the effect of the intervention on a short-term basis, since it might help to prevent long-term problems after MTBI in children and adolescents. In this study, a large sample is recruited for the cohort part. Taking a subset of these participants for the RCT along at the same time enables us to investigate the effectiveness of the intervention faster than waiting on the results of the cohort study first and setting up a new intervention study afterwards. We believe this is an efficient way of investigating this group of participants from an ethical perspective as well. In many studies, various types of TBI (mild, moderate, severe) are included. However, this study investigates activities and participation in children and adolescents with MTBI only. In a study by Ponsford et al. [42], the effectiveness of an early intervention in the form of a general information booklet was evaluated in a mild paediatric population only. However, their study measured the impact of the intervention on reported symptoms, cognitive performance and psychological adjustment and not on preventing activity and participation problems. Furthermore, the sample size of their study was small (*N* = 61) compared with the expected sample size of the present study, and the outcome was measured at 3 months post-injury, while this study measures the outcome at 3 months and 6 months post-injury. The strength of this study is the substantial RCT sample size extracted from a large cohort. Furthermore, the outcome instruments used in this study are based largely on the ICF-CY.

To the authors’ knowledge, this is the first study to examine the effect of an early individualized psychoeducational intervention designed to prevent activity and participation problems in a relatively large group of children and adolescents following an MTBI. All of the participants in the nested RCT design receive usual care, and the intervention group receives an additional intervention. The intervention has a specific theoretical basis, and its design is based on evidence from the literature. Finally, and perhaps most importantly, the intervention is created to suit clinical practice and can be applied easily and directly in daily practice after its effectiveness has been proven. The results of this study will provide insight into which children with MTBI are at risk for long-term participation problems and may benefit from a psychoeducational intervention.

